## Abstract

**Background:**

With over 500,000 annually reported cases worldwide, head and neck cancer (HNC) is the seventh most common type of cancer worldwide. Treatment of HNC with chemoradiotherapy frequently results in serious impairments in physical and psychosocial functioning. Besides, HNC patients typically start their cancer treatment already with poor physical and psychosocial health. It has been shown that a sufficient level of physical activity (PA) before, during, and after cancer treatment is associated with fewer negative treatment-related side effects and a better quality of life (QOL). In order to prevent worsening of functioning and limit the physical impact of the HNC treatment, a comprehensive supervised exercise program (CSEP) may be beneficial during early cancer treatment. However, up to now, the feasibility and effectiveness of such a program are not yet investigated thoroughly in HNC. Therefore, the primary objective of this study is to examine the effectiveness of a CSEP during HNC treatment, in addition to usual supportive care, compared to usual supportive care alone, on health-related QOL up to 1 year post-diagnosis. Secondary objectives entail gathering information on (1) the effectiveness of a CSEP on secondary outcomes such as physical and mental function, activities of daily life, and participation in society and (2) the feasibility, possible barriers, and facilitators for participation in a CSEP during HNC treatment.

**Methods:**

To investigate the effectiveness of the CSEP, a parallel, open-label randomized controlled trial will be performed. To study the feasibility of the CSEP, a mixed-method study will be performed in a subgroup of participants. HNC patients are eligible if they receive radiotherapy at the Radiation-Oncology department of the University Hospital of Leuven. A 4-size permuted block randomization will be used. The control group receives the current standard of supportive care. The intervention group receives a CSEP, additional to the same usual supportive care. The CSEP consists of a 12-week intensive phase with 3 exercise sessions of 1 h per week, where supervision is gradually reduced after 6 weeks. During the maintenance phase (from week 13), patients exercise at home with monthly tele-consultations with a physiotherapist. The CSEP contains supervised aerobic and resistance training. In both groups, outcomes of interest are evaluated through self-reported questionnaires and clinical assessments, at baseline, 6 weeks, 12 weeks, 6 months, and 12 months post-diagnosis. The primary endpoint is health-related QOL, measured with the EORTC QLQ-C30 at 6 months post-diagnosis.

**Discussion:**

The study will be conducted in accordance with the Declaration of Helsinki. This protocol has been approved by the ethical committee of the University Hospitals Leuven (s65549). Recruitment started in January 2022. Results will be disseminated via peer-reviewed scientific journals and presentations at congresses.

**Trial registration:**

Trial Registration: ClinicalTrials.gov

Identifier: NCT05256238

Date of registration: February 25, 2022

## Introduction

### Background and rationale

With over 500,000 annually reported new cases worldwide, head and neck cancer (HNC) is the seventh most common type of cancer worldwide [1, 2]. HNC contains a diverse group of malignancies originating from the mucosa in the oral cavity, nasopharynx, oropharynx, hypopharynx and larynx. Unfortunately, the majority of patients with HNC have locally advanced disease at diagnosis and are, therefore, treated with chemoradiotherapy (CRT) or with radical surgery followed by adjuvant (C)RT. Treatment of HNCs with (C)RT frequently results in serious and persistent impairments in physical and psychosocial functioning [3, 4].

The WHO International Classification of Functioning, Disability and Health (ICF) model offers a framework for understanding disability and health, e.g., during and after HNC [5]. At function level of the ICF, swallowing and speech impairments are specific morbidities experienced in over half of HNC patients at various intensities before, during, and after cancer treatment [3]. Additionally, a large part of HNC patients experience lymphedema, pain, stiffness, and/or weakness of the jaw, neck, and shoulder [3, 4]. These local impairments are mainly caused by radiotherapy-induced fibrosis and neck dissection surgery. All this contributes to activity limitations in neck and shoulder function in about two thirds of HNC patients [3, 4]. More general consequence including fatigue, decreased physical fitness, muscle wasting, and related weight loss are other activity limitations [4–6]. These impairments restrict physical functioning and participation in activities of daily living of many patients, consequently impeding their quality of life [6]. Besides the physical and psychosocial consequences of the cancer treatment, HNC patients typically start their cancer treatment already with poor physical and psychosocial health, compared to healthy controls, and hence, QOL is already impaired prior to starting any intervention [6, 7].

The awareness on the importance of exercise therapy for management of the side effects at the different levels of the ICF during and after cancer treatment in general is increasing rapidly [6–9]. It has been shown that a sufficient level of physical activity before, during, and after cancer treatment is associated with a better prognosis, a lower risk of recurrence, a lower risk of mortality [7–10], fewer negative treatment-related side effects [9], and a better quality of life [8–11]. At this moment, the guidelines of the American College of Sports Medicine recommend 2- or 3-weekly 20–30 min sessions of moderate aerobic exercise plus 2-weekly resistance training at moderate to vigorous intensity (2 sets of 8–15 repetitions at > 60% of the 1 repetition maximum for major muscle groups) to have effect of exercise on health-related quality of life in cancer populations. These guidelines are based on research in mostly breast, prostate, and colon cancer populations as these are the most prevalent populations [8–10].

Up to now, it has not yet been investigated properly whether these general guidelines for exercise programs are translatable to the HNC population. Given the specific physical and psychosocial needs in the HNC population described above, this should be investigated properly [6–9]. In addition, since HNC patients often start their treatment already with poor physical functioning [6], exercise therapy should be initiated at time of diagnosis and continue during and after treatment. In the currently available studies, the outcomes and the content of the exercise programs are very heterogeneous making it difficult to draw conclusions at this moment [8–11]. First, in a pilot study of Zhao S.G. et al. from 2016, HNC patients undergoing concurrent CRT and participating in a program designed to maintain physical activity during cancer treatment maintained or improved function and QOL. They also concluded that the exercise intervention was feasible, thereby providing the basis for larger future interventions with longer follow-up [12]. Second, a study of Samuel et al. (2019) showed that an 11-week structured exercise program for HNC patients receiving CRT helps in improving their functional capacity and quality of life up to 11 weeks after diagnosis [13]. The exercise program consisted of 5 trainings per week, with 7 weeks in the hospital and 4 weeks of home-based trainings. Limitations of this study are that there was no maintenance program and no follow-up period after the 11 weeks.

In addition, next to the effectiveness of an exercise program on different health-related outcomes, barriers and facilitators for participating in a CSEP starting from diagnosis should be properly investigated. In the trial of Samuel et al., patients attend 75% of the prescribed sessions [14]. Unfortunately, specific barriers and facilitators or reasons for non-adhering were not studied. Possibly, the intense schedule of 5 trainings per week may have decreased adherence in that study. Also, it may be interesting to explore whether the combination of in hospital with home-based trainings is more beneficial. Travel time to the hospital is indeed a barrier to exercise, which confirms the need of combining hospital and home-based exercise programs [14].

Given this, a comprehensive supervised exercise program (CSEP) starting early during CRT may be beneficial to prevent worsening of a person’s functioning and limit the physical impact of the treatments for HNC [6–9]. Such a program should consist of a combination of aerobic training, progressive resistance training for all major muscle groups and stretching exercises, in particular in the upper limb region. The program should combine in hospital training with home-based trainings and have a sufficiently long duration.

### Objectives

There is a need to improve the integration of exercise programs into HNC care. The aim is to help HNC patients to prevent decline in and restore physical, mental and social functioning. Currently, no strong evidence is available for a program adapted to the specific needs of HNC patients, in particular during cancer treatment [3, 4, 6]. The primary objective is to examine the effectiveness of a CSEP, in addition to usual supportive care, on health-related quality of life during the treatment of HNC, compared to usual supportive care alone, up to 1 year after diagnosis. This will be performed through an open-label randomized controlled trial.

Secondary objectives entail gathering information on the effectiveness of the CSEP, in addition to usual supportive care on secondary outcome parameters including physical and mental functioning, activity level, and participation level of the ICF. In addition, the feasibility of such CSEP as well as possible barriers and facilitators for participating in a CSEP during HNC treatment will be studied.

### Trial design

A parallel, two-arm, open label trial will be conducted. This single center prospective randomized clinical study will be performed to investigate the effectiveness and the feasibility of a comprehensive supervised exercise program (CSEP) in addition to usual supportive care compared to usual supportive care alone in patients undergoing CRT for HNC, the EffEx-HN trial. This is a superiority trial design because we aim to investigate whether a CSEP is more effective in improving health-related quality of life than the current standard of supportive care. To study the feasibility of the CSEP, a qualitative study will be performed in a subgroup of participants of the large prospective randomized clinical study described above. Quantitative data on feasibility will be collected in all participants.

## Methods: participants, interventions, and outcomes

The SPIRIT guidelines were used [15].

The recruitment of the clinical trial started in January 2022 at the department of Radiation-Oncology of the University Hospitals in Leuven (Belgium). The supervised exercise sessions of the intervention group take place in the exercise room of the department of Physical Medicine and Rehabilitation of the University Hospitals in Leuven (Belgium). A flowchart of the EffEx-HN Trial is provided in Table 1.

**Table 1 Tab1:** Trial flowchart: enrolment, intervention, and assessments of the EffEx-HN trial

Time points	0–1 weeks after diagnosis	*T*_0_ baseline (within 1 week after start of CRT)	*T*_1_ 6 weeks	*T*_2_ 12 weeks	*T*_3_ 6 months	*T*_4_ 12 months
**Enrolment**						
Eligibility screening	X					
Informed consent (intake session)	X					
Randomization	X					
Allocation	X					
**Intervention**						
Start CSEP (IG^a^)		X				
Start maintenance program with monthly tele-consult (IG^a^)				X		
**Assessments**						
Baseline assessment		X				
Follow-up assessments			X	X	X	X
Primary endpoint^b^					X	
Secondary endpoints^c^			X	X	X	X

^a^IG = intervention group ^b^Primary endpoint = 6 months post-diagnosis: primary endpoint for health-related quality of life ^c^Secondary endpoints = 6 weeks, 12 weeks, 6 months, and 12 months post-diagnosis for all outcome measures and 12 weeks for feasibility outcomes

### Patient and public involvement in trial design

The protocol was submitted and approved by the patient support group of HNC patients of the University Hospitals Leuven.

### Eligibility criteria

HNC patients are eligible to participate if they are scheduled for radiotherapy at the Radiation-Oncology department of the University Hospitals Leuven. Inclusion criteria are as follows: (1) ≥ 18 years, (2) diagnosed with primary malignant tumor head and neck region, (3) ECOG performance score 0–1, (4) able to complete baseline assessments prior to start of (chemo)radiotherapy, (5) physically and mentally capable of taking part in an exercise program and motivated to engage in a supervised exercise program. Patients are excluded if one of the following exclusion criteria are present: (1) < 18 years, (2) ECOG performance score ≥ 2, (3) treated with palliative intent, (4) evidence of distant metastases, (5) no basic level of reading and writing in Dutch. Participation of a patient in the study can be discontinued based on the participant’s request or if the disease is worsening, to the extent that exclusion criteria are present (treatment with palliative intent, evidence of distant metastases).

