### Allocation and randomization

A 4-size permuted block randomization is used. The randomization is computer-generated, in particular the allocation to the intervention or the control group is concealed and performed by the randomization module of the Research Electronic Data Capture system (REDCap) before the start of the exercise program, ensuring blinding of the research team [16, 17]. The sequence of randomization is decided by the patient’s record identifier in REDCap, which is received after signing informed consent. An open label study is performed, which means that the therapist/assessor and patients are not masked for the allocation to the intervention or control group. The therapist giving the exercise program and the assessor are the same individual during the entire study period.

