### Sample size

The study was powered to have at least 80% power to detect based on a two-sided test with alpha equal to 0.05 a difference of 10 points in general health-related quality of life measured with the EORTC QLQ-C30 (primary outcome) between both groups at the primary endpoint, i.e., 6 months post-diagnosis. A drop-out of 5%, 10%, and 20% is anticipated at 6 weeks, 12 weeks, and 6 months, respectively. Based on reference values for the EORTC QLQ-C30, a standard deviation of 22.7 was assumed [49]. Further, moderate correlations equal to 0.5 were assumed for the associations with the baseline measurement. Under these assumptions, 75 subjects per group are necessary. The study was also powered on one key-secondary outcome, i.e., the physical functioning subscale of the EORTC QLQ-C30. Since the assumed standard deviation for this subscale was slightly lower (based on the EORTC QLQ-C30 reference values 2008), this has no impact on the required sample size. Otherwise said, with 75 subjects per group, the power is higher than 80% for this secondary outcome, more specific 87.7%.

For the feasibility study, no sample size calculation was performed.

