### Data analysis

#### Effectiveness study

For the general health-related quality of life and the key-secondary outcome (physical functioning subscale), the mean value at 6 months will be compared between both groups after correction for the baseline value. To handle the presence of missing data, this ANCOVA approach will be implemented using a constrained longitudinal data analysis (cLDA) using all collected measurements over time (baseline, 6 weeks, 12 weeks, 6 months, 12 months). Both comparisons will be based on a two-sided test with alpha equal to 0.05.

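### The withdrawal rule for worsening disease can end QOL follow-up as well as exercise, so 6-month values may be missing for reasons the cLDA does not model

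*Protocol article*

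**What the plan says.** The discontinuation rule is the last sentence of Eligibility criteria. Apart from a patient asking to leave, study participation may be ended "if the disease is worsening, to the extent that exclusion criteria are present (treatment with palliative intent, evidence of distant metastases"). Both conditions in the bracket are baseline exclusion criteria from the same section, applied again after randomisation. What may be discontinued is participation in the study. The sentence does not separate stopping exercise from stopping assessment.

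The passages that bear on it:

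- **Primary outcome** (Abstract, Methods): "The primary endpoint is health-related QOL, measured with the EORTC QLQ-C30 at 6 months post-diagnosis".
- **Analysis** (Data analysis, Effectiveness study): 6-month means are compared with correction for baseline. "To handle the presence of missing data", this is done by a constrained longitudinal data analysis (cLDA) on all measurements collected from baseline to 12 months.
- **Planned losses** (Sample size): "A drop-out of 5%, 10%, and 20% is anticipated at 6 weeks, 12 weeks, and 6 months", not split by cause or by arm.
- **Masking** (Allocation and randomization): "the therapist/assessor and patients are not masked for the allocation to the intervention or control group".
- **Rationale** (Background and rationale): sufficient physical activity is associated with, among other things, "a lower risk of recurrence, a lower risk of mortality".

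**The concern.** A rule triggered by prognosis can stop collection of the primary outcome. A patient who develops metastases or moves to palliative treatment before 6 months may have a baseline score and perhaps 6- and 12-week scores, and then nothing.

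The cLDA is valid if, given the QOL scores already observed and the arm, whether a later score is missing does not depend on its value. Here the reason for missingness is disease worsening, and the model as described contains QOL over time but not disease status. Unless earlier QOL already signals the coming change, the model predicts the missing 6-month score from the patient's scores before worsening and from the course of patients who stayed. That prediction is plausibly too high.

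Two features make it possible that the arms differ in such withdrawals. The trial's rationale links activity to recurrence and mortality. The rule is also discretionary, in a trial where the assessor knows the allocation. What is at stake is the 6-month comparison of all randomised patients, and questionnaires never sent cannot be recovered by any later analysis plan.

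**Working it through.** **1. Reproduce the planned size.** Inputs from Sample size: difference 10, SD 22.7, correlation with baseline 0.5, two-sided alpha 0.05, power 80%, 20% drop-out at 6 months.

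- Baseline-adjusted SD = 22.7 × √(1 − 0.5²) = 19.66.
- Per arm = 2 × [19.66 × (1.960 + 0.842) / 10]² = 60.7. Dividing by 0.80 gives 75.8, against the stated 75.
- A cLDA with a common baseline mean, all correlations 0.5 (assumed also between follow-up visits) and stepwise losses of 5%, 10% and 20% gives 80.5% power at 75 per arm and just under 80% at 74.

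The planned 75 per arm is therefore sound. Drop-out enters it only as lost information.

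**2. Standard error of the 6-month difference.** With 60 of 75 observed per arm: 19.66 × √(2/60) = 3.59. From the cLDA calculation: 3.55.

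**3. Bias from the rule.** Let D be how far the unobserved 6-month scores of withdrawn patients lie below the cLDA prediction, taken as equal in both arms. Let q be the share of each arm withdrawn under the rule. Each arm mean is overstated by D × q, so the estimated difference (intervention minus control) is off by D × (q_intervention − q_control). The article gives neither D nor q, so both are assumptions.

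| D (points) | Difference in q between arms | Size of bias (points) |
|---|---|---|
| 15 | 5 percentage points | 15 × 0.05 = 0.75 |
| 20 | 5 percentage points | 20 × 0.05 = 1.0 |
| 20 | 10 percentage points | 20 × 0.10 = 2.0 |

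Against a standard error of 3.59 this is 0.21 to 0.56 standard errors. If there were no true effect, two-sided type I error would be 5.9% at a 1-point bias and 8.6% at 2 points.

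**4. Direction.** With D = 20 and withdrawals of 10% in control and 5% in intervention, the control mean is overstated by 2.0 and the intervention mean by 1.0, so the benefit is understated by 1.0. With the two rates exchanged, the benefit is overstated by 1.0.

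**5. Equal withdrawal.** With q equal in the two arms, the bias under the null is zero. If in addition patients who worsen gain nothing from the programme, the effect in all randomised patients is 10 × (1 − q): 9.5 at q = 5% and 9.0 at q = 10%, while the model would still estimate about 10.

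**The case against.** The rule is permissive, and the sentence is silent on data collection. This is a journal article, and Data Availability says that the full protocol can be requested. That document may say that questionnaires continue, and sensitivity analyses may stand in an analysis plan. This stands as a limit: loss of the 6-month score is a consequence of the rule as written, not something the article states. The missing sensitivity analysis is not the point here. The point is a stated rule that, followed literally, ends study participation.

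The inputs are also unanchored. Withdrawing 10% of an arm under this rule would be half of the planned 20% drop-out, in patients who enter with ECOG 0–1, without metastases and with curative intent. The cited link between activity and recurrence is an association in cancer generally. It does not show that this programme changes metastasis within 6 months. This too stands, and is why the size is given only as a range under assumptions.

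Three stronger readings are tempting, and the documents do not support them:

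- **That the comparison becomes one among patients free of progression.** It does not. The cLDA uses every score collected, so withdrawn patients still contribute their earlier values in their own arm. The rule is also narrower than progression in general.
- **That the rule demonstrably removes the poorest scores.** Low QOL after metastasis or palliative treatment is plausible, but the article gives no figure for it.
- **That keeping these patients would raise power.** Holding the effect at 10, cutting 6-month missingness from 20% to 15% or 10% moves cLDA power from 80.5% to 82.5% or 84.2%. If the retained patients gain nothing, so that the effect is 9.5 or 9.0, power is about 78.5% or 76.0%, before any rise in SD. A gain is not shown.

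**Conclusion.** The concern holds in limited form. As written, the rule can end collection of the primary outcome for a reason tied to prognosis, and the described analysis handles the gap only through QOL history under missing at random. Pre-withdrawal scores soften the problem but do not remove it.

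Under the assumptions shown, the bias is about 0.75 to 2.0 points. That is 7.5% to 20% of the 10-point target and well under one standard error. Its direction cannot be told from the documents, so a reader should not infer that the rule favours the exercise arm; in the scenario with more control withdrawals it works against it. The rate of such withdrawals, the shortfall and the difference between arms are all assumed.

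This does not invalidate the design or the sample size. It should be fixed because the change is small and the data cannot be recovered later.

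**What to change.** Amend the last sentence of Eligibility criteria so that it treats two things separately:

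- Stopping the exercise programme, which remains a clinical decision and is left as it is.
- Leaving study follow-up. State that patients with metastases or palliative treatment continue to be offered at least the QLQ-C30 at each remaining time point unless they withdraw consent, and are analysed in their randomised arm.

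The means largely exist: Outcomes, Effectiveness study, says most questionnaires are completed at home through a REDCap link. It does not say that the QLQ-C30 is one of them, so the amendment should say by link where possible. Offering this one instrument avoids asking these patients for the full 60-minute set.

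The cost is a short amendment, some burden on patients who are unwell, and some non-response among them. The estimated effect may also come out somewhat smaller or more variable, because it would then reflect all randomised patients. If the full protocol already provides for continued follow-up, bringing the published sentence into line with it is enough.
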